#### Endpoints

The primary study endpoint is treatment completion rate. Secondary endpoints include 3-year disease-free survival, overall survival, compliance, and adverse events defined by the Common Terminology Criteria for Adverse Events v.4.0 [6].

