### Study design and statistical methods

The primary endpoint of this study is treatment completion rate, which is expected to be higher than the treatment completion rate in the ACTS-CC [4] due to alternate-day S-1 administration. Assuming a null hypothesis of 73 % treatment completion and an alternative hypothesis of 83 % treatment completion with one-sided type I error = 0.1 and type II error = 0.2, it was necessary to enroll at least 77 patients in each arm. Assuming 10 % loss to follow-up, we calculated that a total of 170 patients were needed in both treatment arms.

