### Decision principle

At the beginning of the study, we established the decision principle to be used after trial results are obtained. If the treatment completion rate for alternate-day S-1 administration (Arm B) is better than that for daily S-1 administration (Arm A), and if the 3-year disease-free survival and adverse-events rates of Arm B is improved or approximately the same as those of Arm A, then alternate-day S-1 administration will be recommended as adjuvant chemotherapy for stage III R0-resected CRC patients.

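### The decision rule turns similar 3-year disease-free survival into a treatment recommendation, but a trial sized only for completion cannot support a similarity conclusion on disease-free survival

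*Protocol article*

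**What the plan says.** The Decision principle section sets a rule at the start of the study with three conditions joined by 'and'. Arm B must have the better completion rate, and DFS and adverse events must satisfy: "if the 3-year disease-free survival and adverse-events rates of Arm B is improved or approximately the same as those of Arm A". If all are met, "then alternate-day S-1 administration will be recommended as adjuvant chemotherapy for stage III R0-resected CRC patients". The article gives no margin, confidence level or test for the DFS condition.

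DFS is not what the trial was sized for. The Endpoints section makes completion rate primary and lists DFS lower down: "Secondary endpoints include 3-year disease-free survival, overall survival, compliance, and adverse events". Study design and statistical methods bases the size on completion only: "Assuming a null hypothesis of 73 % treatment completion" against "an alternative hypothesis of 83 % treatment completion", with "one-sided type I error = 0.1 and type II error = 0.2". From this, "it was necessary to enroll at least 77 patients in each arm", and then: "Assuming 10 % loss to follow-up, we calculated that a total of 170 patients were needed in both treatment arms". No DFS assumption enters the calculation.

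**The concern.** The consequence of the rule is a treatment recommendation for stage III patients after curative resection, not a decision about further testing. A recommendation of that kind implies that efficacy is not materially worse. The only part of the rule that addresses efficacy is the DFS condition, and the trial was not sized for it.

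The completion endpoint does not fill this gap. According to Treatment methods, both arms use the same dosing bands by body surface area, but Arm B has fewer planned dosing days per week. A lighter schedule may be easier to complete, so better completion does not by itself protect efficacy. At stake is an efficacy conclusion that the data could not carry, drawn under a rule fixed in advance.

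**Working it through.** **1. The plan's own sample size.** Inputs from Study design and statistical methods: 73% versus 83% completion, one-sided alpha 0.10, power 0.80.

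- One-sample arcsine formula against a fixed 73%: n = [(z₀.₉₀ + z₀.₈₀) / (2(arcsin√0.83 − arcsin√0.73))]² = 76.5, so 77. This matches the stated figure.
- With the 10% allowance: 77 × 1.10 = 84.7, so 85 per arm and 170 in total. This also matches.
- Read as a comparison of two arms, the same inputs would need 154 per arm. The present point does not depend on which reading was intended. Either way, DFS plays no part.

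**2. Precision for the 3-year DFS difference.** The article gives no 3-year DFS. The nearest figure is the 30.8% stage III recurrence rate in Background, which has no time point; 1 − 0.308 = 69.2%. I therefore assume DFS of 70% and show 60% to 85%. Equal allocation is inferred from the equal numbers per arm.

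Formula, with equal DFS p in both arms, no censoring and an observed difference of zero: half-width = z × √(2p(1 − p)/n).

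At p = 0.70 and n = 85, the standard error is √(2 × 0.70 × 0.30/85) = 0.0703, and 1.96 × 0.0703 = 0.138.

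| Assumed 3-year DFS | 95% half-width, 85 per arm (points) |
|---|---|
| 60% | 14.7 |
| 65% | 14.3 |
| 70% | 13.8 |
| 75% | 13.0 |
| 80% | 12.0 |
| 85% | 10.7 |

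At DFS 70%, 77 evaluable patients per arm give 14.5 points. With 85 per arm, the trial's own one-sided 0.10 level gives 1.282 × 7.03 = 9.0 points. Censoring would widen all of these.

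**3. Chance of meeting the DFS condition when Arm B is worse.** Assume that an observed deficit of at most 5 points counts as similar. With true DFS of 70% versus 60%, the standard error is √((0.21 + 0.24)/85) = 0.0728. The probability is Φ((−0.10 + 0.05)/0.0728) = Φ(−0.69), about 0.25. For a true loss of 14 points it is about 0.11.

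**4. Size needed to exclude a given loss.** With DFS 70% in both arms and 80% power, n per arm = 2p(1 − p)(z_α + 0.8416)²/margin².

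| Loss to exclude | One-sided 0.025 | One-sided 0.10 |
|---|---|---|
| 5 points | 1319 | 758 |
| 10 points | 330 | 190 |
| 14 points | 169 | 97 |

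All of these exceed 85 per arm, even at the lenient level and the widest margin.

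**5. Planned dosing frequency, from Treatment methods.** Arm A: 28 of every 42 days, so 28/42 × 7 = 4.67 dosing days per week. Arm B: every other day, so 3.5 per week. The ratio is 3.5/4.67 = 75%. Over the planned periods, Arm A has 4 × 28 = 112 dosing days in 24 weeks and Arm B has 196/2 = 98 in 28 weeks, a ratio of 87.5%.

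**The case against.** **The article is a condensed account.** It calls its protocol section a digest, and a full protocol or analysis plan may define similarity and say how the interval is used. This stands as far as it goes. A reader might infer that similarity will be judged by eye, without regard to a confidence interval; the article does not say so, and its silence does not establish it. But the point does not need that inference: the consequence of the rule is stated, and no definition alters what 170 patients can exclude.

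**The 14 points rest on an assumed DFS and a chosen confidence level.** This also stands. The 30.8% is a recurrence rate without a time point, not a 3-year DFS. The figure should always be quoted with its DFS, its confidence level and an observed difference near zero. Over DFS of 60% to 85%, the 95% half-width is still about 11 to 15 points.

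**The rule has three conditions.** A reader might infer that a less effective regimen passes easily. The documents do not support that. The 25% depends on an assumed 5-point tolerance and covers the DFS condition only. On the same assumption, a regimen 10 points worse fails that condition about 75% of the time, and it must also do better on completion and acceptably on adverse events.

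**There is a rationale for preserved efficacy.** Background and Discussion cite experience with alternate-day S-1 in resected gastric cancer. It is relevant but comes from another disease, so the efficacy conclusion in colorectal cancer still rests on this trial.

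**Conclusion.** The concern holds in a limited form. The rule draws a treatment recommendation partly from DFS similarity, and a trial sized only for completion cannot support that conclusion however similarity is defined. With 85 per arm and equal observed DFS, a loss of up to about 14 points would lie within the two-sided 95% interval at an assumed DFS of 70%; at one-sided 0.10 the figure is about 9 points. The 25% chance of meeting the DFS condition with a true 10-point loss is an upper bound on a wrong recommendation, conditional on the assumed 5-point tolerance and DFS of 70% versus 60%.

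The point does not touch the analysis of completion, and it does not show that Arm B is less effective. The lower planned dosing frequency only explains why better completion cannot stand in for evidence on DFS.

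**What to change.** In the Decision principle section, replace the consequence "then alternate-day S-1 administration will be recommended as adjuvant chemotherapy for stage III R0-resected CRC patients" with a conclusion limited to completion and feasibility: a positive result supports further confirmatory evaluation of DFS. State also that the difference in 3-year DFS will always be reported with its two-sided 95% confidence interval and the size of loss that the interval does not exclude.

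A numeric floor on the confidence limit would not rescue the recommendation at this sample size. Requiring the 95% lower limit to lie above −10 points needs Arm B to be observed about 13.8 − 10 = 3.8 points better. With truly equal DFS of 70%, that happens with probability 1 − Φ(3.8/7.03), about 29%.

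The change is one of wording and needs no extra patients. Its cost is a more modest claim after a positive result.

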## Discussion

The feasibility of S-1 treatment as an adjuvant chemotherapy for colorectal cancer was confirmed by ACTS-CC [4], although the protocol treatment completion rate remained 76.5 %. Previously, S-1 alternate-day intake maintained the efficacy of chemotherapy while reducing adverse effects for patients with R0-resected stage II/III gastric cancer [5]. Improvement of chemotherapy completion rate for patients with colorectal cancer will lead to an improved patient prognosis.

Therefore, a randomized phase II trial has been designed to examine the efficacy of alternate-day versus current standard daily S-1 administration as adjuvant chemotherapy for R0-resected stage III colorectal cancer.
